## Abstract

**Introduction:**

COVID-19 may cause severe pneumonitis and trigger a massive inflammatory response that requires ventilatory support. The intensive care unit (ICU)-mortality has been reported to be as high as 62%. Dexamethasone is the only of all anti-inflammatory drugs that have been tested to date that has shown a positive effect on mortality. We aim to explore if treatment with hyperbaric oxygen (HBO) is safe and effective for patients with severe COVID-19. Our hypothesis is that HBO can prevent ICU admission, morbidity and mortality by attenuating the inflammatory response. The primary objective is to evaluate if HBO reduces the number of ICU admissions compared with best practice treatment for COVID-19, main secondary objectives are to evaluate if HBO reduces the load on ICU resources, morbidity and mortality and to evaluate if HBO mitigates the inflammatory reaction in COVID-19.

**Methods and analysis:**

A randomised, controlled, phase II, open label, multicentre trial. 200 subjects with severe COVID-19 and at least two risk factors for mortality will be included. Baseline clinical data and blood samples will be collected before randomisation and repeated daily for 7 days, at days 14 and 30. Subjects will be randomised with a computer-based system to HBO, maximum five times during the first 7 days plus best practice treatment or only best practice treatment. The primary endpoint, ICU admission, is defined by criteria for selection for ICU. We will evaluate if HBO mitigates the inflammatory reaction in COVID-19 using molecular analyses. All parameters are recorded in an electronic case report form. An independent Data Safety Monitoring Board will review the safety parameters.

**Ethics and dissemination:**

The trial is approved by The National Institutional Review Board in Sweden (2020-01705) and the Swedish Medical Product Agency (5.1-2020-36673). Positive, negative and any inconclusive results will be published in peer-reviewed scientific journals with open access.

**Trial registration:**

NCT04327505. EudraCT number: 2020-001349-37.

Strengths and limitations of this studyRandomised controlled clinical trial in compliance with Good Clinical Practice.Safety and efficacy endpoints together with multiple explanatory endpoints.Independent Data Safety Monitoring Board.No placebo, open label.Power calculation is based on early pandemic data and ‘best practice treatment’ have changed during the course of the trial.

## Introduction

### Clinical manifestations and challenges with COVID-19

SARS-CoV-2 was first identified in China in December 2019.^1^ The clinical infectious disease COVID-19 was declared a pandemic by the WHO on 11 March 2020; with more than 46 million confirmed cases and more than 1 million confirmed deaths by 2 November 2020.^2^ Clinical experience from China and Italy was published early and even though the overall mortality is low (3.4%), the numbers from critical care were fearsome.^3–6^ Mortality rates were as high as 90% in patients developing acute respiratory distress syndrome (ARDS) in early reports from Wuhan province. Later reports showed 28-day mortality rates of 61.5% in intensive care unit (ICU) patients with acute respiratory illness.^4^ In a recent retrospective cohort study form Wuhan, 19% of patients needed mechanical ventilation or extra corporal mechanical oxygenation, 26% was admitted to ICU and hospital mortality rate was 28%.^7^ SARS-CoV-2 enters human cells through ACE2 receptors, abundant in lungs, arteries, heart, kidney and intestines, causing a downstream activation of an inflammatory cascade that activates the innate immune system.^8^ A synchronised immune response is vital in the control and resolution of viral infections. In some patients, this activation and resolution is dysregulated, causing a disproportionate reaction, popularly called a cytokine storm.^9^ Acute lung injury (ALI) associated with COVID-19 differs from other described ARDS with rapidly progressing respiratory failure and fibrosis. Even patients who have mild symptoms and survive COVID-19 may have significant changes on pulmonary CT, with diffuse ground glass opacities and crazy-paving pattern and consolidation suggesting severe inflammatory involvement.^10^ Despite enormous efforts, a definite cure seems far away and there is urgent need for effective treatments to reduce morbidity and mortality. Remdesivir, Hydroxychloroquine, Lopinavir and Interferon-β1a have been tested in a total of 11 266 subjects included, none of the drugs have been proven effective according to recently published results from the WHO Solidarity trial.^11^ Corticosteroids were tried early in the pandemic with discouraging results, but recently preliminary results from the RECOVERY-trial showed some reduction in 28-day mortality with dexamethasone, with better effect in severe disease.^12^ The RECOVERY-trial showed a mortality of 41.4% in the control group versus 29.3% in the group that received dexamethasone among patients who needed mechanical ventilation.^12^ A recent systemic overview on ARDS reported mortality rates since 2010: overall mortality rates of in-hospital: 45%, ICU: 38% and 28/30-day: 30%.^13^

### Rationale for the study and explanation of the hypothesis

Macrophages, part of the innate immune system, have become major therapeutic targets in ALI/ARDS. Macrophage activation is involved in the early phase of ARDS.^14^ Alveolar macrophages (AMs) are the gatekeepers of the innate immune system in the lungs.

On activation, they secrete several inflammatory cytokines and chemokines including interleukin-1 beta (IL-1β), interleukin-6 (IL-6) and tumour necrosis factor alpha (TNF-α), to attract T-helper1 (Th1)/T-helper 17 (Th17)-cells, new macrophages and neutrophils. AMs are also responsible for clearing apoptotic neutrophils when the infection resolves. Proteomics involved in the switch from inflammatory macrophage (M1) to resolving or anti-inflammatory macrophage subtype (M2) was recently described in a human study of ALI/ARDS.^15^ Hypoxia inducible factor-1 and factor-2 (HIF-1 and HIF-2) and inflammatory factors such as signal transducer and activator of transcription 3 (STAT3) and nuclear factor kappa-light-chain-enhancer of activated b-cells (NFκB) are important transcription factors involved in macrophage polarisation. How and if it is possible to intervene with this intricate network of redox signalling is not clear.^16^ Hyperbaric oxygen (HBO) has been used for almost a century, initially for decompression sickness (DCS), but it was soon noted that it had several anti-inflammatory effects.^17 18^ Recent evidence from animal studies suggest that HBO ameliorate inflammation in DCS induced ALI through polarisation of macrophages from M1 to M2.^19 20^ HBO has been shown to polarise macrophages from M1 to M2 associated with IL-10 and thereby reduces inflammation,^21 22^ and 30-min HBO ex vivo inhibit monocyte IL-1β and TNF-α.^23^ Patients presenting to hospital with COVID-19 normally have almost a week of mild or moderate flu-like symptoms but on admission often have an isolated hypoxic respiratory failure. Many patients, despite severe hypoxemia do not have dyspnoea or carbon dioxide retention suggesting a diffuse but moderate alveolar oedema and a hypoxic adaptation. Hypoxia is relative to the upregulation of adaptive mechanisms. When medical oxygen is administered for a prolonged period, the adaptive mechanisms are put out of play and might aggravate oxidative stress. HBO will give patients a short burst of oxidative stress and reactivate adaptive responses. The hypothesis of HBO as a safe and effective treatment and possible mechanisms has been previously published.^24–26^ Published case series from China and the USA indicate that HBO in these patients may be safe and beneficial.^27–30^ A propensity-matched control study (n=20) from the USA showed 50% lower mortality and almost two-thirds less need for mechanical ventilation in the HBO-treated group.^31^

HBO has the potential to reduce inflammation, restore normal defence mechanisms and thereby reduce morbidity and mortality in COVID-19 pneumonitis

### Remaining gap of evidence

HBO has been provided as ‘compassionate use’ for COVID-19 and some evidence from small case series and a prospective cohort suggests that it is safe and effective, but this needs to be confirmed in randomised controlled trials. There are concerns regarding oxygen toxicity in already inflamed lungs and the optimal dose and timing are still largely unknown. The multiple explanatory outcome measures in our trial may answer some of these questions. Here we report a summary of our protocol that adhere to International Council for Harmonisation-Good Clinical Practice (ICH-GCP) and Standard Protocol Items: Recommendations for Interventional Trials (SPIRIT) guidelines,^32^ V.4 27 February 2021 of the protocol is available as online supplemental file 1 and substantial amendments will be available on clinicaltrials.gov or by request from the corresponding author. The SPIRIT checklist refers to the full protocol.

10.1136/bmjopen-2020-046738.supp1Supplementary data

### Hypothesis and objectives

The overall hypothesis to be evaluated is that HBO reduce mortality, increase hypoxia tolerance and prevent organ failure in patients with COVID-19 pneumonitis by attenuating the inflammatory response.

The primary objective is to evaluate if HBO reduces the number of ICU admissions compared with best practice for COVID-19. Main secondary objectives are to evaluate if HBO reduces the load on ICU resources, morbidity and mortality in severe cases of COVID-19 and to evaluate if HBO mitigates the inflammatory reaction in COVID-19. Other secondary objectives (in selection) is to evaluate if HBO is safe for SARS-CoV-2 positive patients and staff.

## Methods and analysis

### Study design

Randomised, controlled, phase II, open label, multicentre trial conducted at hospitals with hyperbaric facility and ICU. The trial will investigate the safety and efficacy of HBO for COVID-19 but also multiple explanatory outcomes. The total number of participants will be 200 (100 per group) with a subgroup of 20 subjects for explanatory endpoints where we collect blood for extended immunology. Block randomisation will be performed, stratified by gender and site. The trial consists of nine visits over 30 days after randomisation, each visit consists of three parts; (a) review of medical records since last visit and documentation in the electronic case report form (eCRF), (b) measurements and actions to correct any deviations, (c) HBO treatment, if randomised (visit 1–7 only). A flowchart of the study design is depicted in figure 1. and The Consolidated Standards of Reporting Trials flow chart of the trial is depicted in figure 2.

**Figure 1 F1:**
[figure not shown]
Flowchart of the study design. HBO, hyperbaric oxygen; ICF, informed consent form.

**Figure 2 F2:**
[figure not shown]
The Consolidated Standards of Reporting Trials flow chart of the trial. HBO, hyperbaric oxygen; ICF, informed consent form; ITT, intent-to-treat; PP, per protocol.

### Setting and study subjects

The Sponsor is Karolinska Institute, Sweden and presently three centres in Sweden and Germany are involved. Adult patients with SARS-CoV-2 infection, with at least two risk factors for increased mortality, likely to develop ARDS criteria and need intubation within 7 days of admission to hospital will be screened. After information and signed informed consent, study subjects will be checked for inclusion/exclusion criteria.

The inclusion/exclusion criteria are listed in table 1.

**Table 1 T1:** COVID-19-HBO: overview of inclusion and exclusion criteria

Inclusion criteria	Aged 18–90 years
	PaO_2_/FiO_2_ (PFI) below 200 mm Hg (26.7 kPa) (based on ABG measurement)
	Suspected or verified SARS-CoV-2 infection
	At least two risk factors for increased morbidity/mortality Age above 50 years Hypertension Cardiovascular disease Diabetes or prediabetes Active or cured cancer Asthma/COPD Smoking D-Dimer >1.0 mg/L Autoimmune disease
Exclusion criteria	ARDS/pneumonia caused by other viral infections (positive for other virus)
	ARDS/pneumonia caused by other non-viral infections or trauma
	Known pregnancy or positive pregnancy test in women of childbearing age
	Patients with previous CT verified lung fibrosis more than 10%
	CT-verified or spirometry-verified severe COPD with emphysema
	Contraindication for HBO according to local guidelines*
	Not likely to need ICU admission within 7 days of screening (subjective criteria that may exclude any patients who fulfil the other inclusion criteria but where the treating physician suspect a spontaneous recovery)
	Mental inability, reluctance or language difficulties that result in difficulty understanding the meaning of study participation
	Prisoner
	Unable/risk to move patient to hyperbaric chamber

*Contraindications are described in the Standard Operations Procedure for each centre; generally, includes claustrophobia, pneumothorax, severe COPD.

ARDS, acute respiratory distress syndrome; HBO, hyperbaric oxygen.

### Randomisation

Subjects will be enrolled and randomised consecutively as they are found to be eligible for inclusion in the study. HBO treatment will start within 24 hours of randomisation. Eligible subjects will be randomised in a 1:1 allocation, stratified by site and gender in blocks (blinded to all but the randomising clinical research associated at Karolinska Trial Alliance, KTA) to either HBO or Control. The randomisation sequence is computer-generated using RANDOMIZE.NET.

### Interventions

HBO in addition to best practice compared with best practice

HBO: HBO 1.6–2.4 Atmospheres Absolute for 30–60 min, maximum five treatments first 7 days

Control: best practice treatment for COVID-19

The first HBO treatment will be given within 24 hours after inclusion. Patients with respiratory symptoms admitted to the hospital will be informed and asked to participate. The patients will be included once they fulfil the inclusion criteria and none of the exclusion criteria, but the timing of the HBO treatment will depend on available resources.

### Measurements

After the patient has been informed about the study and if agreement to participate, an informed consent form (ICF) will be signed off before any study specific procedures occur.

During the screening, procedures to assure the patient’s eligibility for the study participation will be performed. Females of childbearing potential will have a serum pregnancy test taken. Demographics, medical history including COVID-19 specific history and review of routine blood tests, secondary infections, viral load, radiology, concomitant medications before inclusion will be recorded. Mean new early warning score (NEWS) for the past 24 hours (three measurements 8, 14, 22±2 hours) will be recorded if available (mean is calculated after data are exported from eCRF at the end of study). Baseline NEWS at inclusion will also be recorded. A physical examination will be performed and a HBO-specific questionary as per local routine will be obtained. Subject will be randomised to either HBO (in addition to best practice) or best practice. Routine chemistry and study-specific blood tests will be collected. A complete list of procedures is listed in table 2.

**Table 2 T2:** COVID-19-HBO: list of procedures

Activity	Visit 1	Visit 2	Visit 3	Visit 4	Visit 5	Visit 6	Visit 7	Visit 8	Visit 9
Day	Day 1	Day 2	Day 3	Day 4	Day 5	Day 6	Day 7	Day 14	Day 30
Screening	x								
Inclusion/exclusion criteria	x								
Pregnancy test if woman of childbearing age	x								
HBO-specific medical history/physical examination	x								
Signed informed consent form	x								
Randomisation	x								
1. Medical history	x								
2. Demography*	x	x	x	x	x	x	x	x	x
3. Concomitant medications	x	x	x	x	x	x	x	x	x
4. NEWS score	x, x, x†	x, x, x	x, x, x	x, x, x	x, x, x	x, x, x	x, x, x	x, x, x	x, x, x
5. Standard/study-specific biochemistry	x	x	x	x	x	x	x	x	x
6. Study-specific CBG/ABG	x, x, x†	x, x, x	x, x, x	x, x, x	x, x, x	x, x, x	x, x, x	x, x, x	x, x, x
7. Plasma (microRNA)	x	x	x	x	x	x	x	x	x
8. CBG/ABG HBO	3x	3x	3x	3x	3x	3x	3x		
9. HBO indicated/planned	x	x	x	x	x	x	x		
10. HBO treatment	x	x	x	x	x	x	x		
11. AE	x	x	x	x	x	x	x	x	x
12. ADR	x	x	x	x	x	x	x	x	x
13. UPTD	x	x	x	x	x	x	x	x	x
14. CPTD	x								x
15. ICU admission		x	x	x	x	x	x	x	x
16. Intubation/mechanical ventilation		x	x	x	x	x	x	x	x
17. ICU mortality		x	x	x	x	x	x	x	x
18. Hospital mortality		x	x	x	x	x	x	x	x
19. Overall mortality		x	x	x	x	x	x	x	x
20. Secondary infections	x	x	x	x	x	x	x	x	x
21. Viral load	x	x	x	x	x	x	x	x	x
22. Staff safety (negative events)	x	x	x	x	x	x	x	x	x
23. Pulmonary CT (check records)	x	x	x	x	x	x	x	x	x
24. Chest X-ray (check records)	x	x	x	x	x	x	x	x	x
25. Chest ultrasound (if available)	x	x	x	x	x	x	x	x	x
26. Extended immunology (n=20)	x			x			x	x	x

CBG/ABG HBO is collected once daily for the first 7 days and if clinically warranted.

All used acronyms and abbreviations are listed in the original protocol (p.9–10, Supplement).

Visit 1–7 is 8-7:59 and visits 8 and 9 are 7 days 8-7:59.

*Visits 2–9 demography check only involves change in DNR status.

†Depending on time of inclusion 1–3 samples/observations will be collected during visit 1 at the specified time points. Additionally, a baseline ABG (if not available from the patient’s medical records) and a baseline NEWS is collected.

### Trial endpoints

The primary endpoint is the proportion of subjects admitted to ICU from day 1 to day 30 based on predefined criteria for ICU admission. Main secondary efficacy endpoints are 30-day mortality, time to intubation, time to ICU admission and mean change in inflammatory response and main safety endpoints are measurement of adverse event (AE) and serious adverse events (SAE). A list of main efficacy and safety endpoints is listed in table 3.

**Table 3 T3:** COVID-19-HBO: trial endpoints

Primary endpoint	The proportion of subjects admitted to ICU from day 1 to day 30, based on at least one of the following criteria: (1) Rapid progression over hours (2) Lack of improvement on high flow oxygen >40 L/min or non-invasive ventilation with fraction of inspired oxygen (FiO_2_) >0.6 (3) Evolving hypercapnia or increased work of breathing not responding to increased oxygen despite maximum standard of care available outside ICU (4) Haemodynamic instability or multiorgan failure with maximum standard of care available outside ICU
Secondary endpoints	(in selection)
Main secondary efficacy endpoints	(1) Proportion of subjects with 30-day mortality, all-cause mortality, from day 1 to day 30.
	(2) Time-to-intubation, that is, cumulative days free of invasive mechanical ventilation, from day 1 to day 30
	(3) Time-to-ICU, that is, cumulative ICU free days, derived as the number of days from day 1 to ICU, where all ICU free subjects are censored at day 30
	(4) Mean change in inflammatory response from day 1 to day 30 White cell count+differentiation Procalcitonin C-reactive protein Cytokines (IL-6) (if available at local laboratory) Ferritin D-dimer LDH
	(5) Overall survival
Safety endpoints	(1) The number of subjects, proportion of subjects and number of events of AE
	(2) The number of subjects, proportion of subjects and number of events of SAE
	(3) The number of subjects, proportion of subjects and number of events of SADR
	(4) Mean change in PaO_2_/FiO_2_ before and after HBO compared with mean variance in PaO_2_/FiO_2_ in the control group during day 1 to day 7
	(5) Mean change in NEWS before and after HBO compared with mean change in daily NEWS in the control group during day 1 day 7
	(6) Number of negative events in staff associated with treatment of subject (eg, contact with aerosol from subject), number of events from day 1 to day 30 or last day in hospital if subject is discharged earlier, or at withdrawal

ABG, arterial blood gas; AE, adverse event; COPD, chronic obstructive pulmonary disease; HBO, hyperbaric oxygen; ICU, intensive care unit; LDH, lactate dehydrogenase; PFI, Ratio of arterial oxygen partial pressure to fraction of inspired oxygen; SADR, suspected adverse drug reaction; SAE, serious adverse events.

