### Statistical analysis

*Power calculation*: the primary endpoint ICU admission is defined by criteria for selection for ICU. We have assumed that 50% of the subjects will have at least one criterion during the course of the study and we aim to reduce the ICU admission rate by 40%, that is, to an ICU admission rate of 30%. To achieve 80% power with type-I error rate of 0.05 (two-tailed), a sample size of 93 subjects per group is required. We plan to enrol 200 subjects into this trial. Interim analyses may decide to recalculate sample-size for the trial.

Sample size calculation was done in nQuery V.7.

Primary and secondary endpoints will be evaluated using the intent-to-treat population (ie, all randomised subjects) and the primary endpoint also using the per protocol population (ie, all randomised subjects with no major protocol violations). All randomised subjects will be included in the safety population. The primary analysis of the primary endpoint will be performed using the Cochran Mantel Haenszel test adjusting for randomisation strata site and gender.

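### As printed, the primary endpoint scores death without ICU admission as a non-event, and the endpoint table and power section disagree on whether admission or meeting a criterion is the event

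*Protocol article*

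**What the plan says.** All references are to the protocol article.

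- **Endpoint.** Table 3 gives the primary endpoint as "The proportion of subjects admitted to ICU from day 1 to day 30, based on at least one of the following criteria", followed by four clinical criteria. Death is not listed as a component.
- **Power section.** Statistical analysis says that "the primary endpoint ICU admission is defined by criteria for selection for ICU" and gives the planning rate as "We have assumed that 50% of the subjects will have at least one criterion during the course of the study". The target is 30%. It continues: "To achieve 80% power with type-I error rate of 0.05 (two-tailed), a sample size of 93 subjects per group is required". Planned enrolment is 200, 100 per group.
- **Analysis.** The primary test is Cochran-Mantel-Haenszel (CMH), adjusted for site and gender, in all randomised subjects.
- **Time-to-ICU.** This main secondary endpoint censors every ICU-free subject at day 30. No exception is made for subjects who have died.
- **Population and conduct.** Ages 18 to 90 are eligible with at least two risk factors. A do-not-resuscitate (DNR) order is not among the exclusions in Table 1. The footnote to Table 2 says that after visit 1 the "demography check only involves change in DNR status". The trial is open label.
- **Hypothesis.** The Abstract says: "Our hypothesis is that HBO can prevent ICU admission, morbidity and mortality by attenuating the inflammatory response".
- **Other endpoints and oversight.** 30-day all-cause mortality, time to intubation and overall survival are main secondary endpoints. A DSMB reviews safety under a charter with stopping rules.

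**The concern.** Death on the ward prevents ICU admission, so it is a competing event for the primary endpoint. Under the Table 3 wording the subject stays in the denominator and is counted as not admitted, which is the favourable result. The time-to-ICU rule goes the same way: a subject who dies early on the ward receives the same value as one discharged well.

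If deaths without ICU admission are equally common in both arms, they create no spurious difference. If they differ, the primary comparison mixes prevention of ICU admission with a change in how subjects fail. A shift from ICU to ward death on HBO would look like benefit. A ward death averted in a subject who then goes to ICU would look like harm. Decisions on ICU transfer and treatment limitation are made by staff who know the allocation, and criteria such as rapid progression leave room for judgement.

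The power section complicates this. If meeting a criterion were itself the event, some subjects who deteriorate and die on the ward would count as events. The two definitions would classify such subjects in opposite ways.

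**Working it through.** **1. The plan's own figure.** Inputs (Statistical analysis): 50% against 30%, two-sided 0.05, 80% power. The pooled-variance formula is

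n = [1.960 × √(2p̄(1−p̄)) + 0.842 × √(p1(1−p1) + p2(1−p2))]² / (p1−p2)²

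With p̄ = 0.40: (1.960 × √0.48 + 0.842 × √0.46)² / 0.04 = (1.358 + 0.571)² / 0.04 = 93.0. The stated 93 per group is reproduced. Power at 100 per group is 82.8%.

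**2. The two definitions side by side.**

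| Subject | Table 3 (admitted) | Power section (meets a criterion) |
|---|---|---|
| Recovers on the ward, no criterion met | non-event | non-event |
| Admitted on a listed criterion | event | event |
| Meets a criterion, dies on the ward | non-event | event |
| Dies on the ward, no criterion recorded | non-event | non-event |

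Two of the criteria refer to failure under the maximum care available outside ICU, which a ward patient can meet. The third row is therefore a real category. The fourth stays a non-event on either reading.

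**3. Effect of a shift with ICU-or-death equal in both arms.** The article gives no ward-death rate, so these rates are assumptions. There are 100 per arm; control has 50% ICU and 5% ward deaths; strata are ignored. The upper-tail probability is

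Φ[(d − 1.960 × √(2p̄(1−p̄)/n)) / √((p1(1−p1) + p2(1−p2))/n)]

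- 5-point shift (HBO 45% ICU, 10% ward deaths; composite 55% in both arms): Φ[(0.05 − 0.1384)/0.0705] = Φ(−1.25) = 10.5% favouring HBO. The other tail adds 0.4%, giving 10.9%.
- 10-point shift (HBO 40% ICU, 15% ward deaths; composite 55% in both arms): Φ[(0.10 − 0.1379)/0.0700] = Φ(−0.54) = 29.4%.

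Exchanging the arms gives the same figures against HBO, so the bias can run either way.

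**4. How far secondary mortality would reveal it.** Take 28% control mortality for illustration; this is the hospital mortality of a cohort cited in the Introduction, not a design assumption. If every shifted subject would otherwise have survived, power at 100 per arm to detect the excess is 12% at +5 points and 32% at +10 points.

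**5. Sample size if the composite were primary.** Keep the 20-point difference and let the same share in each arm die without ICU admission:

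| Share | Composite rates | n per group | Power at 100 per group |
|---|---|---|---|
| 2% | 52% vs 32% | 95 | 82.2% |
| 5% | 55% vs 35% | 96 | 81.6% |
| 10% | 60% vs 40% | 97 | 81.2% |
| 15% | 65% vs 45% | 96 | 81.6% |

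All fit within the planned 200.

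**6. How much a same-direction condition protects.** One million trials were simulated for each scenario in step 3, drawing ICU admission, ward death or neither for 100 subjects per arm and using the uncorrected test. The ICU result was significant for HBO in 11% (5 points) and 31% (10 points). Among those, the composite estimate also favoured HBO in 99% and 89%. The two endpoints share most of their events, so direction alone is a weak filter.

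**The case against.** The endpoint matches the stated primary objective, which is to reduce ICU admissions in a phase II trial. Screening aims at patients likely to need intubation within 7 days and excludes those unlikely to need ICU, so enrolment leans towards subjects for whom admission is the expected route. All-cause mortality is the first main secondary endpoint and the DSMB can see deaths. The article condenses a fuller protocol that is not shown and may hold a rule for deaths. Changing the primary endpoint of an open-label trial after 31 randomisations, a safety analysis at 20 completers and a DSMB meeting would raise its own credibility question.

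Most of this stands as mitigation. It does not remove the point: which events count is part of the endpoint definition, the article prints that definition, and its own power section words it differently.

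Stronger readings that a reader might infer are not supported:

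- **That HBO will look effective by moving deaths to the ward.** No rate of death without ICU admission is given. Recording DNR changes is data collection and does not show that such deaths are expected to be frequent.
- **That the type I error is 29%.** In that scenario ICU admission truly differs, so the test is right about its own endpoint; the inference to benefit is what fails. The scenario also assumes that HBO triples ward deaths, from 5% to 15%. A direct comparison of those ward deaths would have about 66% power, so the shift would probably be noticed.
- **That a composite brings more power.** It does so only if HBO also reduces ward deaths. With equal ward deaths, power at 100 per group falls slightly, from 82.8% to between 81% and 82%.
- **That the sample size is wrong.** It reproduces exactly.

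**Conclusion.** The point holds as an ambiguity and a possible bias. Table 3 makes death without ICU admission a non-event, time-to-ICU follows the same logic, and the power section can be read to count some of those subjects as events. Whether the primary comparison is distorted depends on a between-arm difference in deaths without ICU admission, about which the article is silent. Under the assumed scenarios the chance of declaring a difference with ICU-or-death equal in both arms is about 11% at a 5-point shift and 29% at a 10-point shift, against a nominal 5%. With no difference between arms in such deaths, no spurious difference arises. Mortality as a secondary endpoint and DSMB review are useful but partial: the primary test can be positive without them, and power for a mortality excess of these sizes is low. Replacing the primary endpoint is not required.

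**What to change.** 1. State in one place whether the primary event is being admitted to ICU or meeting a selection criterion, and align Table 3 with the power section.
2. Keep ICU admission as the primary endpoint. Prespecify ICU admission or death from any cause by day 30 as a required key supportive analysis in all randomised subjects, with the same CMH test. Report ICU admission, death without ICU admission and death after ICU admission separately by arm.
3. Make no HBO efficacy claim unless the supportive analysis agrees in direction. Step 6 of the working shows that this is a minimum condition, so print the composite estimate with its confidence interval and the component table beside the primary result.
4. In time-to-ICU, treat death before admission as a competing event, or as an event, and do not censor it at day 30.

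**Cost.** ICU admission, intubation and mortality are already collected (Table 2, rows 15 to 19), so no new data are needed. The price is a short amendment, a little more analysis and a slightly stricter condition for claiming efficacy. The amendment should be settled without sight of outcomes by arm, since 31 subjects are already randomised. If the sponsor chose to make the composite primary, about 95 to 97 per group would be needed under the assumptions in step 5, within the planned 200, but the late change would then have to be justified openly.
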